### Sample size calculation

The primary outcome of this trial is the 6MWT distance (meters). The sample size was calculated for a two-arm parallel randomized controlled trial using the standard formula for comparing two independent means [88]. Assumptions included a two-sided α = 0.05, statistical power (1 − β) = 0.80, a clinically relevant between-group difference (Δ) of 60 m, based on perioperative colorectal cancer studies reporting minimal clinically important differences of approximately 60–75 m in the 6MWT [7], and a standard deviation (σ) of 80 m, consistent with previous randomized prehabilitation trials in similar populations [5,89]. Under these parameters, the estimated requirement was 23 participants per group (n = 46 in total). To account for an anticipated dropout rate of approximately 20%, the final target sample size was increased to 28 participants per group, resulting in a total of 56 participants. This sample size is expected to provide adequate statistical power to detect clinically meaningful differences in functional capacity while mitigating the impact of potential attrition [90].

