### Statistical analysis

All statistical analyses will be performed using the Statistical Package for the Social Sciences (SPSS), version 30.0 (IBM Corp., Armonk, NY, USA). A two-sided p-value < 0.05 will be considered statistically significant for all tests.

Descriptive statistics will be used to summarize the baseline characteristics and outcome variables. Categorical variables will be reported as frequencies and percentages, whereas continuous variables will be expressed as means and standard deviations (or medians and interquartile ranges, as appropriate), together with 95% confidence intervals. The Shapiro–Wilk test will be used to assess the normality of continuous variables. To verify baseline comparability between the two groups, parametric or non-parametric tests will be selected based on data distribution: t-tests or Mann–Whitney U for continuous variables, and Chi-square tests for categorical variables.

To evaluate the effect of the intervention over time, linear mixed-effects models will be applied to account for within-subject correlations in longitudinal data. The primary models will include participant-level random intercepts, with time modeled as a categorical fixed effect, together with group and the group-by-time interaction. The covariance structure will be selected on the basis of model fit and parsimony. Random slopes for time will be explored in sensitivity analyses if supported by model fit and data structure. Prespecified adjustment variables beyond the main fixed effects will include the stratification factors used in randomization, namely age and sex. When significant interaction effects are observed, Bonferroni-adjusted post hoc tests will be used to identify pairwise differences.

Between-group comparisons at each time point will be conducted using analysis of covariance (ANCOVA), adjusting for baseline values (T1). Differences in categorical outcomes will be analyzed using the Chi-square test or Fisher’s exact test, as appropriate.

All analyses will be conducted under the intention-to-treat (ITT) principle, including all randomized participants in the groups to which they were originally assigned, regardless of adherence or protocol deviations. Missing data will be handled using multiple imputation under a missing-at-random assumption, with the imputation model incorporating treatment group, time, baseline measures, and other variables associated with missingness, as appropriate.

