## Discussion

The main objective of this randomized controlled trial is to evaluate the effectiveness of an asynchronous telerehabilitation program delivered through the HEFORA digital platform, across both the prehabilitation and postoperative recovery phases, compared with a booklet-based usual-care program reflecting the perioperative pathway routinely available in the study setting before trial implementation. The study responds to the growing clinical need to mitigate perioperative deterioration while addressing the logistical and geographic barriers that often limit access to center-based rehabilitation programs. By integrating multimodal components into a home-based, digitally supported protocol, this trial proposes a patient-centered strategy that may improve continuity of care during one of the most vulnerable phases of the oncologic trajectory.

The 6MWT was selected as the primary outcome because it is a valid and clinically meaningful measure of functional capacity in surgical and oncology populations. Its clinical relevance is supported by consistent associations between improvements exceeding the minimal clinically important difference (MCID) and reduced postoperative morbidity and shorter hospital stays [5,91,92]. By assessing this variable at four perioperative time points, this study acknowledges the dynamic and non-linear functional trajectories described in patients with CRC [92]. At the same time, performance in the 6MWT may reflect not only physiological adaptation but also motivation, engagement, familiarization, and confidence fostered by ongoing support. Accordingly, any between-group differences in walking performance should be interpreted as potentially arising from a combination of physiological and behavioral mechanisms. To reduce the risk of differential assessment bias, performance-based outcomes will be administered by a blinded assessor using the same standardized instructions and procedures in both groups at each time point. This interpretation is further strengthened by the inclusion of additional objective outcomes, including muscle strength, spirometry, body composition, and ultrasound-based muscle assessment.

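### No single test decides the primary 6MWT result: unadjusted visit-by-visit ANCOVAs repeat, without protection, contrasts that the primary mixed model tests with a gate and Bonferroni

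*Protocol article*

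**What the plan says.** - **Primary outcome.** The Sample size calculation section states: "The primary outcome of this trial is the 6MWT distance (meters"). Neither there nor under Primary outcome is a visit named.
- **When it is measured.** The Discussion refers to the 6MWT as follows: "By assessing this variable at four perioperative time points". The Procedure section makes T5 a telephone contact. The walk test is therefore done at T1 to T4, with three post-baseline comparisons.
- **Sizing.** The sample size was obtained "using the standard formula for comparing two independent means". The inputs are: "Assumptions included a two-sided α = 0.05, statistical power (1 − β) = 0.80"; "a clinically relevant between-group difference (Δ) of 60 m"; and "a standard deviation (σ) of 80 m". This is one comparison, with no visit attached.
- **Threshold.** The Statistical analysis section sets one rule: "A two-sided p-value < 0.05 will be considered statistically significant for all tests".
- **Route one.** The same section gives mixed models with group, categorical time and their interaction, adjusted for age and sex, and labels them primary. Bonferroni-adjusted post hoc tests follow when the interaction is significant.
- **Route two.** A separate paragraph then states: "Between-group comparisons at each time point will be conducted using analysis of covariance (ANCOVA), adjusting for baseline values (T1"). It contains no condition on the interaction, no adjustment and no supportive or sensitivity label.

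**The concern.** A group difference in 6MWT distance at T2, T3 or T4 can reach the report by two routes. In the mixed model it has to pass the interaction test and a Bonferroni correction. In the ANCOVA at the same visit it has only to reach p < 0.05. The unprotected route undoes the protection of the other.

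The primary label on the mixed models does not settle this, because it names a model and not a deciding quantity. The group term, the interaction and the pairwise contrasts all remain candidates.

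The visits also answer different questions. T2 is the day before surgery and reflects prehabilitation only. T3 is day 21 after surgery, before rehabilitation starts. T4 follows the whole programme. A positive T2 and a positive T4 would be different claims, and the text lets either be presented as the primary finding. At stake is whether the headline claim carries the 5% error rate for which the trial was sized.

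**Working it through.** **The plan's own figure.** The protocol states no error rate across visits. Its one related figure is 23 per group, for a single two-mean comparison. With its stated two-sided inputs, n = 2(z₀.₉₇₅ + z₀.₈₀)²σ²/Δ² = 2 × (1.960 + 0.842)² × 80²/60² = 2 × 7.85 × 1.778 = 27.9, so 28 per group and not 23. That is a separate matter. It neither supports nor weakens this point, since the false-positive rate hardly depends on n.

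**Inputs.**
- From the protocol: two arms 1:1, four 6MWT visits, three post-baseline ANCOVAs adjusted for T1, each test at two-sided 0.05, SD 80 m, and 23 per group (28 with the dropout allowance).
- Assumed, not in the protocol: between-visit correlations of 0.5 to 0.8, either exchangeable (the same for every pair of visits) or decaying with distance between visits (first-order autoregressive).
- Assumed decision rule: any one significant result may be read as a positive primary outcome.

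**Simple bounds.** Three independent tests give 1 − 0.95³ = 0.143. With Bonferroni, 1 − (1 − 0.05/3)³ = 0.049. The 14.3% is a reference for the three ANCOVAs only. It is not a ceiling once the interaction test is added.

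**Simulation under no effect** (20,000 trials per scenario). At each post-baseline visit, distance is regressed on T1 distance and group, and the group coefficient is tested on N − 3 degrees of freedom. The group-by-time test is the random-intercept F test on 3 and 3(N − 2) degrees of freedom. Age and sex are left out.

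| Correlation | n per group | Any of 3 ANCOVAs | Any ANCOVA or interaction | ANCOVAs read only after significant interaction | 3 ANCOVAs, Bonferroni |
|---|---|---|---|---|---|
| Exchangeable 0.5 | 23 | 0.1338 | 0.1475 | 0.0371 | 0.0466 |
| Exchangeable 0.7 | 23 | 0.1278 | 0.1391 | 0.0351 | 0.0424 |
| Exchangeable 0.8 | 23 | 0.1262 | 0.1384 | 0.0389 | 0.0449 |
| Decaying 0.5 | 28 | 0.1304 | 0.1540 | 0.0340 | 0.0464 |
| Decaying 0.7 | 28 | 0.1234 | 0.1493 | 0.0360 | 0.0431 |
| Decaying 0.8 | 28 | 0.1184 | 0.1444 | 0.0435 | 0.0448 |

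The ungated rate is about 12-14% for the ANCOVAs and about 14-15% with the interaction. In the decaying scenarios the interaction test alone rejects in 5.8-6.9% of trials, because a random intercept does not fit that correlation pattern. This accounts for part of the combined figure there. Gating the ANCOVAs on the interaction, or applying Bonferroni to them, brings the rate below 5% in every row.

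**Wider range.** Across exchangeable correlations of 0 to 0.9 and decaying correlations of 0.5 to 0.9, the combined rate runs from 13.2% to 16.0%. The assumed correlation therefore matters little; the reading of the ANCOVA sentence matters a great deal.

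**The case against.** **The ANCOVAs may be meant as part of the gated sequence.** The ANCOVA sentence follows directly on the interaction-then-Bonferroni sequence, so it could describe how those between-group comparisons are made, or be secondary to the primary models. On the gated reading there is no inflation. This stands as a possible intention, but the text does not state it: the sentence is in its own paragraph, has no condition, and falls under a threshold set for all tests.

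**The decision rule is not the protocol's.** Nowhere does it say that one significant ANCOVA makes the trial positive. That is correct, and the 14-15% is conditional on it. But nothing in the text excludes it, because no deciding result is named.

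**Detail may sit in a statistical analysis plan.** A full hierarchy is commonly left there, and that plan is not shown. The point rests only on rules that this article itself fixes: the threshold, the limited scope of Bonferroni, and the ANCOVAs at each visit.

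**Stronger readings that the document does not support.** A reader might infer that no analysis has any precedence. That is wrong, because the mixed models are labelled primary. A reader might also infer that a favourable visit could be chosen and the others left out. The protocol plans comparisons at every visit, defers analysis until all assessments are final, and commits to dissemination whatever the direction or significance of the results. The remaining risk is which visit is emphasised as the primary result, not hidden selection.

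**Conclusion.** The point holds in a conditional form. The protocol names a primary model but no deciding term, contrast or visit for the 6MWT, and its visit-by-visit ANCOVAs lie outside both the interaction gate and the Bonferroni rule.

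Taken literally, with any one result allowed to count, the false-positive rate is close to three times nominal (about 14-15% against 5%). If the ANCOVAs are gated, it is below 5%. The figures rest on assumed between-visit correlations and on the decision rule given above. It would be wrong to report 14-15% as the trial's established error rate. What is established is that the text permits both readings and does not choose between them, for the one outcome on which the trial was sized.

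**What to change.** Before database lock, and documented as such:

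1. Name one decisive primary test at two-sided 5%. One well-supported option is the between-group difference in 6MWT distance at T4, the end of the full programme, from a single baseline-adjusted model with age and sex. It is not the only sound choice: the group-by-time test, or another single contrast that the sponsor justifies, would also do.
2. Label the other visits as supportive. Report them with 95% confidence intervals and no significance claim, or adjust them by Holm or Bonferroni.
3. Label the separate ANCOVAs as sensitivity analyses, or drop them. If they were meant to be the post hoc tests after a significant interaction, say so and bring them under the Bonferroni rule.
4. Tie the sample-size paragraph to the chosen contrast and visit.

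The cost is a few sentences and no new data. The price is that the non-primary visits lose confirmatory status.

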### Allocation and blinding

Participants will be randomly assigned in a 1:1 ratio to either the IG or CG using computer-generated block randomization (www.randomizer.org), stratified by age and sex. Allocation will be concealed using sequentially numbered, opaque, sealed envelopes handled by an independent researcher not involved in the intervention or outcome assessment.

All participants will be assigned a unique identification code to ensure confidentiality. The outcome assessor will be blinded to the group allocation, and the researcher conducting the intervention will not be involved in any assessment procedures, preserving single-blind conditions.

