#### Secondary outcomes.

Secondary outcomes are prespecified as either key supportive secondary outcomes, including muscle strength, body composition, pulmonary function, and health-related quality of life, or as exploratory and implementation-focused outcomes, including physical activity, sleep quality, psychosocial variables, treatment expectancy, usability, satisfaction, and adherence. This distinction is intended to enhance interpretability and to clarify that not all secondary endpoints are meant to support confirmatory inference to the same extent.

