#### Physical activity level (IPAQ-SF).

Self-reported level of physical activity will be assessed using the International Physical Activity Questionnaire – Short Form (IPAQ-SF). This validated tool is widely used in clinical and epidemiologic research to quantify habitual physical activity in adults and to monitor changes in response to health interventions [60,61].

The IPAQ-SF consists of seven items that measure the frequency and duration (minutes per day and days per week) of physical activity performed in the past seven days across three intensity domains: vigorous activity, moderate activity and walking, and time spent sitting. The answers will be used to calculate total physical activity in minutes per week (Metabolic Equivalent Task, MET-min/week) and allow categorization into low, moderate or high physical activity according to the IPAQ scoring protocol [60].

This questionnaire has shown acceptable reliability and validity for the assessment of physical activity levels in cancer survivors and perioperative patients [62,63]. In the context of CRC rehabilitation, physical activity monitoring is critical to understanding behavioral adaptations, adherence to exercise recommendations, and their potential associations with clinical recovery, functional outcomes, and QoL.

The IPAQ-SF will be administered at each of the five time points (T1–T5), allowing longitudinal analysis of changes in physical activity levels during the intervention and follow-up periods.

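### Categorical outcomes get plain chi-square or Fisher tests that ignore the T1 category, any ordering and the age and sex strata, and the per-visit ANCOVAs omit the strata; a baseline-adjusted ordinal model would be more efficient where a T1 value exists

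*Protocol article*

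**What the plan says.** Three statements in the Statistical analysis section bear on this.

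- Mixed models: "Prespecified adjustment variables beyond the main fixed effects will include the stratification factors used in randomization, namely age and sex".
- Continuous outcomes, visit by visit: "Between-group comparisons at each time point will be conducted using analysis of covariance (ANCOVA), adjusting for baseline values (T1"). Age and sex are not listed.
- Categorical outcomes: "Differences in categorical outcomes will be analyzed using the Chi-square test" or Fisher's exact test, as appropriate. No baseline value, ordering or stratum is named.

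Allocation and blinding describes "computer-generated block randomization (www.randomizer.org), stratified by age and sex".

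The clearest candidate for the categorical sentence is in the IPAQ-SF section. The answers give a continuous MET-min/week total and also "allow categorization into low, moderate or high physical activity according to the IPAQ scoring protocol". The same section says "The IPAQ-SF will be administered at each of the five time points (T1–T5"), so a T1 category exists. The Secondary outcomes section places physical activity among the "exploratory and implementation-focused outcomes, including physical activity, sleep quality, psychosocial variables".

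**The concern.** The plan accepts T1 adjustment for continuous per-visit comparisons and stratum adjustment for the mixed models, then drops both for categorical outcomes. For a three-level ordered outcome, Pearson chi-square spends 2 degrees of freedom on unordered differences and sets aside the participant's own T1 category. With at most 28 per arm, that is information the trial will hold and not use.

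Two practical consequences follow. One questionnaire could give a T1-adjusted answer for its continuous score and an unadjusted answer for its categories, and the two could differ. The effect sizes listed at the end of the Statistical analysis section (Cohen's d and r) do not suit a comparison of categories, so such an outcome might be reported with a p-value and no estimate.

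This is a stated method, not a detail left to a document that is not shown.

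**Working it through.** **1. The plan's own figures.** The protocol gives no power, effect size or T1 correlation for any categorical outcome, so there is no figure to reproduce. Its only sample-size inputs are for the 6MWT: difference 60 m, SD 80 m, two-sided 0.05, power 0.80, stated as 23 per group and raised to 28 for dropout. From these inputs, 2 × (1.960 + 0.842)² × 80² / 60² = 27.9, so 28 evaluable per group rather than 23. That is a separate matter. Here 23 and 28 serve only as plausible arm sizes.

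**2. Assumptions not in the protocol.** Three equally likely levels from a latent normal variable; latent shift of 0.4 to 0.75 SD (0.75 is 60/80, borrowed from the 6MWT); latent T1-to-follow-up correlation of 0 to 0.7; age and sex effects of 0.15 SD each.

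**3. Three-level outcome.** Simulated power in %, 500 replicates per row, simulation error about 2 points per estimate. The proportional-odds model adjusts for T1 category, age and sex.

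| n/arm | effect (SD) | corr. | chi-square | ordinal, unadjusted | proportional odds, adjusted | gain over chi-square |
|---|---|---|---|---|---|---|
| 23 | 0.60 | 0.3 | 34.6 | 43.4 | 50.4 | 16 |
| 23 | 0.75 | 0.3 | 51.6 | 61.8 | 68.6 | 17 |
| 23 | 0.60 | 0.5 | 35.2 | 44.6 | 52.6 | 17 |
| 23 | 0.75 | 0.5 | 51.8 | 61.2 | 70.8 | 19 |
| 23 | 0.60 | 0.7 | 35.0 | 42.8 | 62.2 | 27 |
| 23 | 0.75 | 0.7 | 51.0 | 61.2 | 80.0 | 29 |
| 28 | 0.60 | 0.3 | 43.2 | 51.8 | 57.4 | 14 |
| 28 | 0.75 | 0.3 | 57.0 | 66.6 | 73.2 | 16 |
| 28 | 0.60 | 0.5 | 39.8 | 48.8 | 60.2 | 20 |
| 28 | 0.75 | 0.5 | 58.4 | 70.2 | 78.2 | 20 |
| 28 | 0.60 | 0.7 | 39.2 | 48.8 | 73.6 | 34 |
| 28 | 0.75 | 0.7 | 61.0 | 70.6 | 86.8 | 26 |
| 28 | 0.40 | 0 | 20.4 | 22.2 | 25.2 | 5 |
| 28 | 0.40 | 0.3 | 21.2 | 25.8 | 31.6 | 10 |
| 28 | 0.40 | 0.5 | 22.0 | 25.0 | 32.0 | 10 |
| 28 | 0.40 | 0.7 | 22.4 | 27.0 | 40.6 | 18 |

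At 0.6 to 0.75 SD the gain is about 14 to 30 points, with one cell at 34. Using the ordering alone accounts for about 8 to 12 of these. Most of the rest comes from the T1 category. Age and sex add 0 to 3 points over T1 alone, within simulation error.

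The adjusted test is slightly liberal at this size (null rejection 4.8 to 7.8% at 28 per arm), so its gains are somewhat overstated. A cross-check by linear-score ANCOVA on the category (1,500 replicates, null rejection about 4 to 5%) gave 10 to 12 points at correlation 0.3 and 15 to 19 at 0.5. At 0.7 with 23 per arm it gave 25 to 30. At 0.4 SD it gave 4 to 17.

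**4. Binary cut.** With 23 per arm, a cut at 0 and a 0.75 SD shift, the proportions are 0.50 and Φ(0.75) = 0.77. The smallest expected count is (11.5 + 5.2)/2, about 8, so Pearson chi-square is the natural choice. Exact enumeration gives 49.4% power for chi-square (null rejection 5.4%) and 37.7% for Fisher (2.6%). Logistic regression adjusted for the T1 category gave 52, 55 and 58% at correlations 0.3, 0.5 and 0.7 in one simulation, and 53 to 62% in another. The gain over chi-square is therefore about 3 to 9, or 4 to 13, points.

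**5. ANCOVA without the strata.** Noncentral t, n = 23 per arm, T1 correlation 0.5, d = 0.75/√[(1 − 0.5²)(1 − R²)], where R² is the share of residual variance explained by age and sex. Power is 0.819 at R² = 0, 0.838 at 0.05 and 0.857 at 0.10, a gain of about 2 to 4 points.

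**The case against.** The strongest reply is that no affected endpoint is named. The chi-square sentence lists no outcome, and nowhere does the protocol say which outcomes are analysed as categories. The IPAQ-SF also yields MET-min/week, which can go through the mixed model and the T1-adjusted ANCOVA. The HADS bands and the PSQI cut-off are described as customary thresholds, not declared as analysis variables. Satisfaction and adherence have no T1 value, so an unadjusted test is defensible there. All of this stands, and it makes the concern conditional.

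The reply on importance also stands for the most part. Physical activity, sleep and psychosocial outcomes are classed as exploratory. The EQ-5D dimensions, five ordered levels within a key supportive outcome, would be an exception, but only if they are compared as categories. Under randomisation chi-square remains a valid test, and chance T1 imbalance is already in its error rate. A reader might infer bias or an inflated false-positive rate; the documents do not support that. The issue is efficiency.

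Two other inferences go too far. One is a large gain for binary cut-offs, from setting Fisher at about 38% against adjusted logistic regression at 53 to 62%. Most of that gap is Fisher's conservatism, and the plan allows chi-square where appropriate. The other is that ignoring the strata drives the loss; age and sex contribute little.

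One could also read the age and sex sentence as covering every analysis. It sits with the mixed models, and the ANCOVA sentence lists T1 only, so the text does not settle it. None of these replies justifies leaving T1 and the ordering out where both exist.

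**Conclusion.** The concern holds as a conditional point about efficiency. As written, any ordered categorical outcome with a T1 value would be compared without its baseline, its ordering or the strata, out of line with how the same section treats continuous outcomes.

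For three levels the loss is about 14 to 30 points of power at 0.6 to 0.75 SD and T1 correlations of 0.3 to 0.7, with the low end nearer 10 to 12 in the better-calibrated cross-check. At 0.4 SD it is about 5 to 18 points over correlations of 0 to 0.7. For a binary cut it is about 3 to 13 points. The strata are worth about 0 to 4 points, so the case for adding them is mainly consistency with the stratified randomisation.

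A reader might infer a fixed double-digit power loss for this trial. The documents do not support that: the effect sizes, correlations and category splits are assumptions, the largest effect is borrowed from the 6MWT, and no outcome is tied to the chi-square sentence. The primary 6MWT analysis is unaffected.

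**What to change.** Replace the categorical sentence with wording such as: 'Ordered categorical outcomes with a T1 value will be compared by proportional-odds (binary: logistic) regression adjusted for the T1 category, age and sex, reported as odds ratios with 95% CIs; chi-square or Fisher tests are kept for outcomes without a T1 value and for sparse tables.' Extend the ANCOVA sentence so that it adjusts for T1, age and sex.

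The cost is two sentences and standard SPSS procedures, with no new data. The Data management section defers analysis until all assessments are final, so the change can be made before results are seen. Regression coefficients also pool directly under the planned multiple imputation, which a Fisher p-value does not.

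The downsides are a proportional-odds assumption, possible sparse cells and slight liberality at this sample size, and 2 degrees of freedom in the ANCOVA.
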